### Analysis plan

Analyses are planned and supervised by the trial statistician (AD). Study eligibility and enrollment will be summarized according to the CONSORT statement [106]. Descriptive statistics of baseline variables will be assessed by intervention arm. Analyses will be based on the intention-to-treat population, thus including data from all participants who provide baseline data and are subsequently randomized to one of the two trial conditions. Missing follow-up data will be imputed using multiple imputation methods. For the primary analysis, a mixed, linear, repeated-measurement ANCOVA will be conducted, with alcohol initiation (in the form of an initiation index) as the dependent variable; group, time, and interaction between group and time and recruitment center as fixed effects; baseline scores of alcohol use as covariates; adolescent and intervention groups within the study arm as random effects; and time as a repeated effect. The contrast between both groups at the 18-month follow-up will be assessed in a confirmatory manner. We will report adjusted group differences with corresponding 95% confidence intervals (CIs), *p* values, and Cohen’s *d* effect sizes. A systematic examination of factors associated with loss to follow-up will be conducted. The two-sided type I error will be set at 5%. An additional analysis will be conducted on a per-protocol data set as sensitivity analysis. A further sensitivity analysis will be carried out using the data set with all available cases (without any imputation of missing data). The secondary outcomes as well as a potential moderating role of individual and family-level variables and adherence to the intervention and engagement in home practice will be examined in an exploratory manner with appropriate methods. The other model parameters will be set as in the primary outcome analysis. The safety endpoints will be determined using frequency tables and, if possible, using mixed logistic regressions to compare the event frequencies. Interim analyses are not planned. A detailed statistical analyses plan will be prepared and finalized before the code is broken. Statistical analyses will be carried out with SPSS Version 23 or newer (IBM Corp., Armonk, NY, USA).

Mechanisms of action and subgroup analyses will be identified within the wider consortium (see “Trial governance”) using structural equation models with Mplus Version 5 or newer [107]. These methods require larger data sets [108]. Therefore, we will employ standardized measures for central variables across the consortium and collapse data sets from five clinical trials on mindfulness-oriented interventions in different populations for sufficient statistical power. We will explore potential mediators of intervention effects with a focus on experimental measurements of self-regulation (i.e., Monetary Incentive Delay Task, Stop Signal Task, Cambridge Gambling Task), mindfulness skills (i.e., Mindful Awareness and Attention Scale, MAAS), and emotion regulation (i.e., Difficulties in Emotion Regulation Scale, DERS).

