### Randomization procedure and blinding

Enrolled families will be randomized in a 1:1 allocation ratio into both intervention groups (SFP or SFP-Mind), as per a computer-generated randomization schedule stratified by recruitment center and intervention cycle. Multiple recruitment centers will be used for the trial. As soon as there are sufficient consenting participants for a single intervention cycle of seven sessions (typically six to eight families per intervention arm), the following random allocation process will be applied. First, an independent statistician will be informed by the study team about the sample size of participating families in the designed intervention cycle and create a concordant computer-generated randomization sequence, which will be concealed until assignment occurs. Second, a researcher independent to the study team will receive an anonymized index identification code for each family participating in that intervention cycle, including information on absolute time restrictions for participation (i.e., holidays, carers’ weekday absences), from the study team. The independent researcher will then randomly assign an index identification code to the randomized sequence. In the case that a defined time restriction of one family means incompatibility with the randomly allocated intervention timing, the family will be allocated to the other intervention arm by the independent researcher. This methodology is necessary to ensure family participation as some might have fixed time constraints to participate. In the event of reallocation due to individual time restrictions, the index identification code will be separately reported to the study team after the allocation process is finalized to allow for methodological scrutinization. See Additional file 2 for a flow chart of randomization procedures.

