### Interventions

#### SFP 10–14 (control)

Families in the control group will participate in the standard SFP 10–14, which is a highly structured and evidence-based prevention program for families at the universal prevention level [27]. ›*Familien stärken*‹ is the certified German version, which relies on a video/DVD-based approach to learning the same as the original US program. In the narrated videos, participants see typical family interactions in diverse families and settings. To accommodate a contemporary urban setting and to increase authenticity and credibility, in extensive pilot work the original US-version video material was presented and discussed in focus groups of target families and translated as well as culturally adapted [68]. The program features seven weekly sessions of approximately 3 h. Per session, three group facilitators simultaneously work with 8–12 families, with parallel sessions for parents and adolescents during the first hour and sessions for the entire families during the second hour. All sessions include DVD presentations, role-plays, group discussion, input, social bonding, and skill-building activities. At the end of the program, a family meal is also provided to strengthen support and sharing between families. For more information on program content, see Bröning et al. [69].

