### Methods against bias

We take the following action to minimize potentials for biased results. Assessments will be conducted by trained interviewers unaware of the study condition, at home and individually in separate rooms for participating family members to ensure privacy and confidentiality and to reduce drop-out. Blinding of families and intervention facilitators is not possible. To maintain program retention, during the family sessions we offer child care for families who have younger siblings they cannot leave at home alone [69]. Moreover, participating families will be financially rewarded for complete program retention and for each completed follow-up data collection. To avoid crossover in the intervention groups, we aim for implementation of parallel group training with regard to both intervention conditions.

Data management will be performed locally following the guidelines of Good Clinical Practice (GCP) and will be monitored (including source data verification), collected, and preprocessed by the Clinical Trial Center North, thus an external clinical research organization (CRO).

A Data and Safety Monitoring Board (DSMB) will be implemented once the recruitment has started with regular meetings (preferably by telephone conferences), with an open and closed part with and without the coordinating investigator. The DSMB will monitor study and recruitment progress, protocol deviations, loss-to-follow-up data, serious adverse events (SAE) and adverse events (AE), and all problems of the study and decide independently from the coordinating investigator whether the study can be continued or a recommendation is given to change the design or stop the trial. The members of the DSMB will be experienced scientists who are not otherwise involved in the study, independent of the investigators and the trial sponsor, and will have no conflict of interests.

Recruitment centers and all researchers conducting the consenting process and baseline assessments will be repetitively trained to conceal any information which could lead the participants to associate an intervention timing with an intervention arm in order to improve allocation concealment.

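### Randomisation is stratified by center and cycle, but the primary model has no cycle term; if cycles differ within centers, the 18-month contrast loses some precision

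*Protocol article*

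**What the plan says.** **Randomisation procedure and blinding.** "Enrolled families will be randomized in a 1:1 allocation ratio into both intervention groups", using a "computer-generated randomization schedule stratified by recruitment center and intervention cycle". A new sequence is drawn once enough families have consented for one cycle, "typically six to eight families per intervention arm". Methods against bias adds that "we aim for implementation of parallel group training with regard to both intervention conditions". One cycle therefore normally yields one SFP 10–14 group and one SFP-Mind group, drawn from the same families.

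**Analysis plan.** The primary model has "group, time, and interaction between group and time and recruitment center as fixed effects", baseline alcohol use as covariate, and "adolescent and intervention groups within the study arm as random effects". The test that counts is named: "The contrast between both groups at the 18-month follow-up will be assessed in a confirmatory manner". Of the two stratification factors, only center is in the model.

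**The concern.** The trial blocks on cycle but does not analyse by it. The random effect for intervention group looks as if it covers the gap, but it is nested in arm. It lets each group have its own level and takes the two groups of a cycle as independent. Anything those groups share, such as season, calendar period or referral source, is then counted as variation between groups and enters the standard error of the arm contrast. By design it should cancel, because both arms occur in every cycle.

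What is at stake is precision: a confidence interval wider than the design earns, and some lost power. The protocol lists the model terms explicitly, so this concerns something stated, not a detail left open.

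**Working it through.** **1. The plan's own figure.** With d = 0.40, 80% power, two-sided 5% and r = 0.30 (Sample size section), the normal approximation is n = 2(1.96 + 0.84)²(1 − 0.30²)/0.40², which gives 90 per arm. The noncentral t gives power 0.799 at 90 and 0.803 at 91, hence 91. Then 91/0.85 = 107.1, so 108 per arm and 216 in total. The stated sample size reproduces. It takes families as independent.

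**2. Inputs.** Taken from the protocol: 216 families, 182 of them analysed, and 6–8 families per arm per cycle. At 7 per arm there are 216/14 = 15.4 cycles, and 91/15.4 = 5.9 analysed families per arm per cycle. Assumed, because the protocol gives neither: group variance rg = 0.02 of the total, and residual cycle variance rc from 0 to 0.10.

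**3. Formulas.** With k cycles and m analysed families per arm per cycle:

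- true variance of the contrast: (2/k)[rg + (1 − rc − rg)/m]
- variance under the planned model: (2/k)[rc + rg + (1 − rc − rg)/m]

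The SE ratio is the square root of the second over the first. Example at rc = 0.05: 0.02 + 0.93/5.9 = 0.178; adding 0.05 gives 0.228; √(0.228/0.178) = 1.13. The actual two-sided alpha is 2[1 − Φ(1.96 × ratio)]. Power uses d = 0.40, with the variance multiplied by 1 − 0.30².

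| rc | SE ratio | Actual alpha | Power, cycle accounted for | Power, planned model |
|---|---|---|---|---|
| 0 | 1.00 | 0.050 | 0.770 | 0.770 |
| 0.01 | 1.027 | 0.044 | 0.774 | 0.758 |
| 0.02 | 1.053 | 0.039 | 0.778 | 0.745 |
| 0.05 | 1.132 | 0.027 | 0.789 | 0.707 |
| 0.10 | 1.261 | 0.013 | 0.808 | 0.640 |

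These are large-sample figures that ignore degrees of freedom and any absorption of cycle by center.

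**4. Simulation closer to the stated model.** Center fixed, 5 centers × 3 cycles (assumed), 6 analysed families per group, rg = 0.02, the 18-month contrast alone, and variance components estimated by balanced ANOVA and held at zero or above.

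| rc | Type I, planned | Type I, random cycle | Power, planned | Power, fixed cycle | Power, random cycle |
|---|---|---|---|---|---|
| 0 | 4.3% | 4.8% | 72% | 69% | 74% |
| 0.02 | 3.7% | 4.6% | 70% | 70% | 73% |
| 0.05 | 2.9% | 4.6% | 67% | 71% | 73% |
| 0.10 | 1.9% | 4.2% | 61% | 73% | 74% |

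At rc = 0.01, power is 71% planned, 70% fixed cycle and 74% random cycle. Planned against random cycle, the loss is 74 − 71 = 3 and 73 − 70 = 3 points at 1% and 2%, 73 − 67 = 6 at 5%, and 74 − 61 = 13 at 10%. The formula in step 3 gives 1.6 and 3.3 points at 1% and 2%. A gap of 2 points already appears at rc = 0. It comes from holding variance components at zero or above, not from the missing block, so the low end of the range should be read as small.

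**5. Limiting case.** With one cycle per center, the fixed center effect is the cycle effect. Simulated results with and without fixed cycle terms are then identical.

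**The case against.** The strongest reply is that the harm is conditional. It needs centers that run several cycles and variance left over after center and baseline use, both of which the model already contains. The protocol states neither the number of centers nor any cycle variance. Recruitment lies in one region over about 12 months, which limits calendar differences. At 1–2% the effect is slight. This stands, and the point is worded accordingly.

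A reader might infer that the planned standard error is definitely too large, or that the whole shortfall of the type I error below 5% comes from the missing term. The documents support neither. Planned type I error is already about 4.3% with no cycle variance at all.

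The number of cycles is also uncertain. The description of the control program says that "three group facilitators simultaneously work with 8–12 families", which would mean about 9 to 13 cycles instead of 14 to 18. Larger groups raise the ratio somewhat: with 12 families per group (10.1 analysed) and rc = 0.05, √[(0.05 + 0.02 + 0.93/10.1)/(0.02 + 0.93/10.1)] = 1.20. Fewer cycles also make fixed cycle terms dearer. Neither changes the direction.

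Finally, the protocol promises a detailed analysis plan before the code is broken. That leaves room to add the term, but the model as listed does not contain it.

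**Conclusion.** The mismatch between strata and model is plain in the text. Its consequence is a possible, one-sided loss of efficiency. If residual cycle variance is 1–2%, 5% or 10% of the total, the standard error is about 3–5%, 13% or 26% too large, and about 2–3, 6 or 13 points of power are lost against a random-cycle model. The standard-error figures rest on about 15 cycles, 5.9 analysed families per group and a group variance of 2%. The power figures rest on the simulated layout of 5 centers with 3 cycles each and 6 families per group. The cycle variance, the group variance and the layout of centers are assumptions.

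It would be wrong to read this as a threat to validity. The error is conservative: the arm contrast is not biased and false positives do not increase. The sample-size arithmetic is untouched. If cycles do not differ, or each center runs one cycle, omitting cycle costs nothing. This is a minor efficiency gain available almost free.

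**What to change.** Add intervention cycle, nested in recruitment center, to the primary model as a random effect. Keep center fixed and keep the random effect for intervention group within arm. Use Satterthwaite or Kenward–Roger degrees of freedom, and write this into the analysis plan before the code is broken.

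Do not replace center with fixed cycle terms. In the simulation they cost 72 − 69 = 3 points of power when cycles do not differ, and only break even at about 2% cycle variance. The random-cycle version lost no power at any setting tried, and its type I error stayed below 5%.

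The cost is one term in the model statement. Cycle is known for every family because allocation is made within it, so no new data are needed.

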### Setting and recruitment

Recruitment shall take place at community-based child and family service institutions in the region of Hamburg, Germany, which will be chosen as recruiting centers if they reach a sufficient amount of families with their own qualified preventive service programs. As the SFP 10–14 is not routinely implemented in Hamburg, we will set up the required infrastructure for recruitment and program implementation in cooperation with and with support from the local authorities, as we have done for a similar study in the past [34]. Multiple recruitment strategies will be employed to reach a sufficient number of recruitment centers; recruitment includes distribution of written information and presentation of the program goals and study procedures by project representatives via local professional networks and specified agencies in the family health care and social service sector. Additionally, we will start initiatives to raise awareness in educational settings and at authority-level meetings.

Potential referrers will be informed about all aspects of the study and will agree to deliver both program versions in accordance with the study procedures, particularly those that concern randomization procedures, ethical standards, and qualified intervention delivery. Referring institutions will recruit potential participants and inform them about the prevention programs and the study procedures. Consent to participate in the family program (experimental or control) will take place prior to the baseline assessment. Interested families will be visited by a member of the research team for subsequent eligibility assessment and enrolment into the study. Written informed consent, with emphasis on withdrawal rights and ethical aspects as well as all relevant conditions of trial participation, will be obtained during the family visit. Baseline data will be collected before randomization. Trial participants are subsequently randomized to one of the two trial conditions. Recruitment/trial inclusion will be ongoing over a period of approximately 12 months. Figure 1 displays the anticipated CONSORT participant flow.

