One goal is to stimulate mindfulness practice outside the weekly program sessions. Participants will thus be strongly encouraged to practice meditation and MT on a daily basis and to protocol their practice on diary cards. Parents will be instructed to support adolescent home practice. Moreover, home practice MT-related content, such as guided meditations, will be provided in written form as well as in audio files and a computer/smartphone app. This material will be specifically developed for study purposes and serves as a practical and user-friendly method to foster home practice of program content. Importantly, the app is therefore not designed to collect data (however, frequency of use of app content will be analyzed). Use of the app is voluntary, as not every child may have access to a tablet or smartphone, and will be fully compatible with German regulations of data security. Existing integrations of (parent-directed) mindfulness training into the SFP 10–14 [64, 65] indicate that facilitating mindfulness practice via didactic presentations about principles of mindfulness, modeling of mindfulness practices, and group interactive discussions are feasible formats to accommodate a family-based substance use prevention setting. Additional file 1 provides a schematic overview of the experimental and control interventions.

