### Baseline assessments and follow-ups

Study outcomes for adolescents and their parents/carers will be assessed by trained research staff blinded to the intervention condition at the families’ homes. Participants will be surveyed at baseline (prior to randomization), post intervention (approximately 8 weeks after baseline), as well as 6 months and 18 months (follow-ups) after post assessment. Fidelity and adherence data (i.e., ratings of training sessions) will be gathered during the intervention period (7 weeks). Figure 2 shows an overview of measures from study participants at each time point.

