### Implementation outcomes

For the participants in the SFP-Mind group only, we will assess mindfulness practice using several questions about sustained use of mindfulness practice in the follow-up assessments. In both intervention groups, we will also assess the following variables:
Program satisfaction: participants (parents and adolescents) will rate how satisfied they are with the program based on the Treatment Satisfaction Questionnaire (*Fragebogen zur Beurteilung der Behandlung*, FBB) [104] (A + P)Trainer adherence to principles and concepts of mindfulness will be rated according to a purpose-designed rating scale based on the MBI:TAC (Mindfulness-Based Interventions—Teaching Assessment Criteria) proposed by Crane et al. [105]Ongoing mindfulness practice (formal (e.g., meditation of deep breathing) and informal mindfulness practices; purpose designed; analysis of home practice diary and evaluation of frequency of app use) (A + P)

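### Adherence and home practice arise after randomisation and depend on the arm, so they cannot serve as moderators of the randomised effect

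*Protocol article*

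**What the plan says.** The protocol article's Analysis plan gives individual and family-level variables a possible moderating role and, in the same sentence and the same role, says that "adherence to the intervention and engagement in home practice will be examined in an exploratory manner". It leaves the methods open but adds: "The other model parameters will be set as in the primary outcome analysis". The primary model contains group, time, their interaction, recruitment center and the baseline alcohol score, with random effects for adolescent and intervention group.

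The timing is given elsewhere. Setting and recruitment says: "Baseline data will be collected before randomization". Baseline assessments and follow-ups says: "Fidelity and adherence data (i.e., ratings of training sessions) will be gathered during the intervention period (7 weeks".

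Home practice of mindfulness is described under SFP-Mind (experimental intervention): "Participants will thus be strongly encouraged to practice meditation and MT on a daily basis and to protocol their practice on diary cards". The audio files and the app appear in the same section. Implementation outcomes begins "For the participants in the SFP-Mind group only, we will assess mindfulness practice" through questions on sustained use at follow-up. It then lists ongoing mindfulness practice, the home practice diary and app use among the variables assessed in both groups.

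Intervention fidelity explains that independent raters score adherence from videotapes of selected sessions against a list of prescribed activities, modified for the new mindfulness content.

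**The concern.** A moderator of a randomised effect has to be a characteristic that allocation cannot change. Only then are families with the same moderator value in the two arms comparable. Adherence and home practice do not meet this condition: both occur after allocation, and what they measure depends on the program delivered.

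The trial asks whether mindfulness training adds value to an active program. A finding that SFP-Mind works better in families who practise more would be read as support for mindfulness, most readily if the randomised contrast were null. Families who practise more may differ in ways that also affect adolescent drinking, and randomisation gives no protection against that.

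**Working it through.** **1. The plan's own figures.** The Sample size section gives d = 0.40, r = 0.30, two-sided 5%, 80% power and 91 per arm. The residual SD is √(1 − 0.30²) = 0.954. Power from the noncentral t is 79.9% at 90 per arm and 80.3% at 91, so 91 per arm (182 in total) reproduces. For dropout, 91/0.85 = 107.1, rounded up to 108 per arm, or 216. These figures do not depend on the present point; d = 0.40 serves only as a yardstick.

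**2. What a practice interaction would estimate.** Write the index as Y = a + b·G + c·P + e·(G×P) + covariates, with G = 1 for SFP-Mind and P = practice.

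- *P recorded only in SFP-Mind.* Controls have no value. If they are left out, there is no between-arm comparison. If they are set to P = 0, then G×P equals P on every row, c and e cannot be separated, and only c + e is estimable. That sum is the practice slope within SFP-Mind, which is not a moderation effect.
- *P recorded in both arms.* The term can be fitted, but P is still measured after allocation. It reflects response to an assigned daily task in one arm and something else in the other, so equal values of P do not mark comparable families.

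**3. Adherence.** Under the article's definition this is rated delivery, a property of sessions and training groups and not of families. The list of activities differs by arm, so the scale does too, and delivery quality is not randomised. A group-by-adherence term compares unlike quantities.

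**4. Illustration of size, for practice.** The correlations are assumptions; none comes from the documents. Suppose neither arm nor practice has any effect, and a family trait correlates ρp with practice and −ρy with the index. The practice-outcome correlation is then −ρp·ρy. With a median split of normally distributed practice, the mean of the upper half is √(2/π) = 0.798 SD, so the expected difference of the high-practice half from control is −0.798·ρp·ρy. The simulated columns come from 4,000 null trials per row with 92 families per arm (216 × 0.85 / 2 = 91.8).

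| ρp / ρy | Formula, high half vs control (SD) | Simulated, high half | Simulated, low half | Within-arm slope with p < 0.05 |
|---|---|---|---|---|
| 0 / 0 | 0 | 0.00 | 0.00 | 5% |
| 0.3 / 0.3 | 0.798 × 0.09 = 0.07 better | 0.07 better | 0.07 worse | 14% |
| 0.5 / 0.3 | 0.798 × 0.15 = 0.12 better | 0.12 better | 0.12 worse | 30% |
| 0.5 / 0.5 | 0.798 × 0.25 = 0.20 better | 0.19 better | 0.20 worse | 67% |

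The simulation did not adjust for baseline. Adjustment for the baseline index would remove whatever part of the trait that index captures, and no more.

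**The case against.** The strongest reply is that the analysis is exploratory, the methods are left open, a detailed analysis plan is to follow, and the article writes down no group-by-practice term. A within-SFP-Mind association would be compatible with the text. Part of this stands: no confirmatory conclusion is at risk, and the exact model may be settled in a document not shown. But the article itself gives these variables a moderating role and carries over the between-arm settings. The exploratory label addresses how much weight a result gets; it does not remove bias from the choice of variable.

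Three stronger readings are tempting, and the documents do not support them:

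- *That home practice belongs only to SFP-Mind.* The SFP-Mind section and the opening of Implementation outcomes point that way, but the list that follows covers both groups. The description of the control program does not mention home practice either way, and the schematic comparing the two programs is in an additional file that is not shown. What can be said is that the sections disagree.
- *That any better-with-practice result would be a pure artefact in favour of mindfulness.* It would be confounded, but could be partly real. The direction is also open: the Ethics section expects that families of children with behavioral difficulties may be more willing to take part. If such families also practised more, the bias could run against SFP-Mind.
- *That motivated families select themselves into high adherence.* This would apply to attendance, but the article defines adherence as session ratings. The objection to adherence as a moderator then rests on its timing and its arm-specific scale.

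**Conclusion.** The point holds in a limited form. Using adherence or home practice as moderators in a model built on the primary between-arm analysis would give an effect that is either not estimable or confounded, and that could not be interpreted as moderation or dose-response. This follows from the timing and arm-dependence of the variables and needs no numerical assumption.

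The size does need assumptions. With trait correlations of 0.3 to 0.5 and no true effect, the spurious advantage of high practisers over control is about 0.07 to 0.20 SD, at most half of d = 0.40 (0.20/0.40). The gap between high and low practisers within SFP-Mind is twice that, 0.14 to 0.40 SD. A reader might infer from the upper end that selection could reproduce the whole planning effect. That would set a within-arm gap against a between-arm effect, at the most extreme of the assumed values, and is not a fair comparison.

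The confirmatory 18-month contrast and the 182/216 calculation are not touched.

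**What to change.** 1. In the Analysis plan, limit moderator analyses to variables measured before randomisation.
2. Report home practice and adherence separately, as within-arm associations adjusted for the baseline alcohol index, behavioural difficulties (SDQ) and family functioning (Family APGAR), provided the last two are scheduled at baseline (the schedule figure is not shown). Label them non-causal and do not call them moderators. The false-positive rates in the table are for exactly this kind of association, so the label matters.
3. Say which adherence is meant, rated delivery or family attendance.
4. Reconcile Implementation outcomes, which both restricts practice questions to SFP-Mind and lists practice, diary and app use for both groups, with the SFP-Mind section.

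A complier-average analysis is not a good substitute. Both arms offer seven sessions with comparable contact, so arm is a poor instrument for sessions attended. If treatment is redefined as SFP-Mind sessions, the exclusion assumption is doubtful against an active control.

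The cost is a change of wording before the analysis plan is finalised, with no new data beyond those already planned. The downside is that the practice result can no longer be presented as effect modification.
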